### Power calculation

Since this study is planned as a pilot study, formal statistical power calculations are not performed for all measures and tests of interest. The primary limitation for making power calculations is the lack of available information on what would constitute a clinically significant effect size for the measures of interest in OAT. Thus, we refer to other studies (regarding osteoarthritis of the knee and ultrasound therapy) for a “sample size calculation” since there is no justification with regard to statistical power [34, 35, 44]. The parameters determined with this pilot study will be used to plan the number of cases in a subsequent controlled prospective randomized trial. However, we estimated a sample size of 45 patients per group and defined a two-sided significance level of 0.05 for all tests. We expect a dropout rate of approximately 10% and therefore plan to enroll 50 patients per group, or a total of 150 patients.

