### Data analysis

The data collected are described using statistical parameters. Continuous data are described with mean, standard deviation, minimum, maximum and 95% confidence intervals; for categorical data, the frequencies attained and the associated percentages are given with 95% confidence intervals.

The statistical analysis will only include the patients who complete the study in accordance with the protocol. Sub-collectives can be examined exploratively if this makes sense after the survey has been completed. In addition to the primary analysis of the comparison of patients with and without ultrasound therapy, there is a comparison of the patients between the different groups.

Group differences (MHT versus TUS versus study group with MHT + TUS) regarding the primary endpoint are analyzed with the non-parametric Kruskal-Wallis test for independent samples. After the global test, the groups are compared in pairs (Mann-Whitney tests). Secondary endpoints are evaluated according to the scaling of the data but are also always tested non-parametrically. The evaluation of intra-group differences (DASH or other characteristics after 9, 13, 17, and 33 weeks) is carried out by means of a nonparametric analysis of variance for repeated observations (Friedman test). In line with the nature of the pilot study, no adjustment is made for multiple testing. A *p* < 0.05 is considered (in the exploratory sense) to be statistically significant. Missing values will be replaced using multiple imputation [45]. All occurring AEs (AEs and SAEs) are described individually.

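### Arms are compared on DASH by rank tests alone, with no baseline-adjusted between-group difference or confidence interval, although the pilot is meant to supply figures for sizing the next trial

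*Protocol article*

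**What the plan says.** The Data analysis section of the protocol article fixes the between-group method. Differences among the three arms on the primary endpoint "are analyzed with the non-parametric Kruskal-Wallis test for independent samples", and Mann-Whitney tests then compare the arms in pairs. For the other outcomes: "Secondary endpoints are evaluated according to the scaling of the data but are also always tested non-parametrically". The course over the four follow-up visits is assessed within each group by a Friedman test. Continuous data are described by mean, SD, range and 95% confidence interval. The section calls the comparison of patients with and without ultrasound the primary analysis and names no test specific to it.

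Under Outcome parameters, the primary outcome is change in DASH from baseline at weeks 9, 13, 17 and 33. The Abstract instead gives the DASH score after 6 months. The visit schedule (Table 1) has DASH, SF-36, pain VAS, key pinch force and goniometry at baseline and at all four later visits.

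On purpose, the Power calculation section states: "The parameters determined with this pilot study will be used to plan the number of cases in a subsequent controlled prospective randomized trial".

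**The concern.** The design collects a baseline and four later values of every efficacy outcome, but the only between-group analyses named are rank tests. These take no baseline covariate and no longitudinal structure. The Friedman test uses the repeated measures, but it works inside one arm and cannot compare treatments.

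Two things are at stake. The first is precision: baseline DASH usually predicts later DASH, and adjusting for it tightens the comparison without another patient or visit. The second is output. To size a later trial, the most useful results of this one are the estimated contrast between arms, its confidence interval, and the residual SD after baseline adjustment. As described, the tests deliver p-values and the descriptive tables deliver per-arm summaries. None of the three quantities is named.

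No SAP is at hand, and details of reporting may stand there. The choice of test, however, is stated in the article and can be judged as it stands.

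**Working it through.** **1. The plan's own figure.** The section says "we estimated a sample size of 45 patients per group", with a "dropout rate of approximately 10% and therefore plan to enroll 50 patients per group, or a total of 150 patients". 45 / (1 − 0.10) = 50 per group, and 3 × 50 = 150. This reproduces. The 45 itself cannot be re-derived, because no effect size, SD or power is given; the section says that "there is no justification with regard to statistical power".

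**2. Inputs for the comparison.**
- From the article: 45 evaluable patients per group and two-sided 0.05.
- Assumed: baseline-to-follow-up DASH correlation r from 0.3 to 0.8, equal variances at baseline and follow-up, and, for power only, a true difference of 0.5 SD of the follow-up score.

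**3. Variance per patient**, in units of the DASH variance:
- follow-up score alone (the Abstract's endpoint): 1
- change from baseline (the Methods endpoint): 2(1 − r)
- baseline-adjusted (ANCOVA): 1 − r²

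ANCOVA relative to change is (1 − r²) / [2(1 − r)] = (1 + r)/2. ANCOVA relative to the follow-up score alone is 1 − r².

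| r | ANCOVA / change | Reduction | n per group by ANCOVA matching 45 by change | ANCOVA / follow-up score |
|---|---|---|---|---|
| 0.3 | 0.65 | 35% | 45 × 0.65 = 29.3 | 0.91 |
| 0.5 | 0.75 | 25% | 45 × 0.75 = 33.8 | 0.75 |
| 0.7 | 0.85 | 15% | 45 × 0.85 = 38.3 | 0.51 |
| 0.8 | 0.90 | 10% | 45 × 0.90 = 40.5 | 0.36 |

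The gain over a change score shrinks as r rises. The gain over the follow-up score alone grows, from 9% to 64%.

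**4. Against the rank tests actually planned.** The ratios above compare ANCOVA with a parametric analysis of change. For the planned tests, take the Mann-Whitney efficiency under normality (0.955), so the effective n is 45 × 0.955 = 43.0. Pairwise power is then approximately Φ(0.5 / √(2v/n) − 1.96), with v the per-patient variance.

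| r | Rank test on change | ANCOVA |
|---|---|---|
| 0.3 | 50% | 70% |
| 0.5 | 64% | 78% |
| 0.7 | 85% | 91% |
| 0.8 | 96% | 98% |

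A rank test on the follow-up score alone has 64% at any r. Worked example at r = 0.5: for the rank test on change, √(2 × 1/43.0) = 0.216 and 0.5/0.216 − 1.96 = 0.36, which gives 64%. For ANCOVA, √(2 × 0.75/45) = 0.183 and 0.5/0.183 − 1.96 = 0.78, which gives 78%.

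**5. What an estimate would show.** With 45 per group, the 95% half-width of a pairwise difference is 1.96 × √(2/45) = 0.41 SD of the variable analysed. For ultrasound (two arms, 90 patients) versus none (45 patients) it is 1.96 × √(1/45 + 1/90) = 0.36 SD. Intervals this wide are what a planner needs to see, and a p-value does not show them.

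**The case against.** The strongest reply is that this is an exploratory pilot with bounded questionnaire scores, and a consistently non-parametric approach is defensible. Allocation is randomised and the rank tests keep their type I error, so nothing is invalid. That stands. Several stronger readings are tempting, and the article does not support them:

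- A reader might infer that the arms are tested visit by visit. The Data analysis section lists the four weeks only for the within-group analysis and does not say which value enters the Kruskal-Wallis test.
- A reader might say that baseline and repeated measures are wasted. Under Outcome parameters the endpoint is change, so baseline enters by subtraction, and the Friedman test uses the later visits. The use is inefficient, not absent.
- A reader might fear bias from chance baseline imbalance, since no stratification is described. Randomisation and the test's sampling distribution already allow for such imbalance; adjustment buys precision.
- A reader might say that the pilot yields nothing for planning. The descriptive means and SDs give a crude difference and a raw SD. They do not give the interval for the contrast or the adjusted residual SD.
- A reader might hold that rank tests cannot be combined with the stated multiple imputation. They can be pooled, and how to do so is a matter for the SAP. A model estimate merely pools more directly.

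It is also true that the size of the gain rests on a correlation found nowhere in the article. Finally, the Kruskal-Wallis test addresses the three-arm comparison, while the comparison labelled primary is ultrasound versus none, so a remedy confined to the three pairs would miss it.

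**Conclusion.** The point holds as one of efficiency and estimation. The article names no baseline-adjusted comparison, no longitudinal comparison between arms, and no between-group difference with a confidence interval, and this fits poorly with its aim of sizing the next trial.

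The variance given up relative to a change score is about 10% (r = 0.8) to 35% (r = 0.3), assuming equal variances. If the Abstract's endpoint applies, it is 9% to 64% over the same range. These figures illustrate the possible gain and are not properties of this trial. The power figures also assume normality and a 0.5 SD difference. The absence of a named contrast estimate does not depend on any of these assumptions.

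**What to change.** Add to the Data analysis section a baseline-adjusted model for DASH. Either of two forms would do:

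- ANCOVA at week 33 with arm and baseline DASH; or
- a repeated-measures model with arm, visit, arm-by-visit and baseline DASH, reporting the week 33 contrast.

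State that week 33 is the Abstract's 6-month time point. It lies 33 − 9 = 24 weeks after the end-of-intervention visit, which is how I read it.

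Report adjusted mean differences with 95% confidence intervals for ultrasound (groups B and C together) versus none (group A), the comparison the section calls primary, and for the three pairs of arms. Report the residual SD and the observed baseline-to-follow-up correlation, so that the next trial can be sized from them. Analyse pain VAS, SF-36, pinch force and range of motion in the same way, each with its own baseline. Keep the Kruskal-Wallis and Mann-Whitney tests as sensitivity analyses.

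The cost is a paragraph of wording and slightly more programming; trial conduct does not change. The model relies on approximate linearity and well-behaved residuals. These should be checked by residual diagnostics or covered by robust standard errors, because agreement with a rank test checks neither.

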**Methods:**

This study is a single-center, randomized, controlled, parallel-group pilot trial. One hundred fifty patients with rhizarthrosis and current disease activity will be randomized to one of three conservative interventions over 6 months. Interventions are (1) multimodal hand therapy (2) therapeutic ultrasound, and (3) combination therapy with both hand therapy and ultrasound therapy. The primary outcome measure is the Disabilities of the Arm, Shoulder, and Hand (DASH) questionnaire score after 6 months. Secondary endpoints are changes in pain, quality of life, disability progression, and changes of hand function. Safety will also be assessed.

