## Introduction

Rhizarthrosis (or osteoarthritis of the trapeziometacarpal joint) (OAT) is a common form of osteoarthritis in the hand leading to chronic disability in humans over 50. Although the exact mechanisms of osteoarthritis are still elusive, various person-level risk factors are recognized [1–9]. Although the hand X-ray is the gold standard for diagnosing and monitoring OAT, it has limited correlation to clinical symptoms [2, 10, 11]. The prevalence ranges between 4 and 36% depending on the diagnostic criteria used, rises sharply at ages over 60, and is thought to be twice to four times higher in women [2, 9–13] . OAT leads to articular cartilage damage, adjacent tissue degeneration, and may result in total joint destruction. Moreover, OAT is a major cause of progressive disability, early retirement, and depression in adults [8, 14, 15]. Currently, there is no cure for OAT, but several surgical therapies are available, with or without alloplastic reconstruction, which may improve function und reduce pain [16, 17]. However, they all may have substantial side effects, failure rates, and patients respond differently due to the complex nature of the disease. Therefore, conservative options should be considered first [18]. Consequently, there is a need for conservative therapies such as specific hand therapies that may reduce OAT symptoms, improve the patient’s quality of life, and, at best, delay disease progression [19]. It is unclear which conservative measures, if any, are most effective [20]. The aim of conservative treatment is to restore thumb functionality, including pain relief, stability, motility, and strength. Treatments commonly used prior to surgery include injections (cortisone, hyaluronate), analgesics, patient education in joint protection, strengthening exercises, assistive devices, and orthotics [21, 22]. Few randomized clinical trials on conservative treatment of OAT have been published [22–27]. There is increasing evidence favoring multimodal manual treatment to reduce pain and ameliorate function in OAT patients [26, 28–30]. For more than 60 years, therapeutic ultrasound (TUS) has been a non-invasive method to treat musculoskeletal pain, soft tissue injuries, and chronic wounds with debatable efficacy [31, 32]. However, recently TUS was reported to improve function, tissue regeneration, and relieve pain via thermal and non-thermal mechanisms in osteoarthritis of the knee [33–36]. Experimental data suggest that TUS treatment might prevent degenerative changes of the meniscus and exert a reparative effect via activation of cartilage growth factors [37]. Despite such evidence of efficacy, to the best of our knowledge, TUS has never been studied in OAT. Despite this lack of proven efficacy, based on our clinical experience, physiotherapists frequently use TUS to treat rhizarthrosis. It is of interest that TUS was used as a harmless, non-invasive ‘sham procedure’ in nontherapeutic doses in several clinical studies in OAT [20]. The aim of the present study is (1) to provide a direct comparison of the efficacy of two promising and readily available conservative treatment methods for symptomatic OAT, namely multimodal hand (MHT) therapy and TUS, (2) to suggest treatment recommendations, and (3) to offer direction for future studies. This research is expected to have a positive impact on OAT patients, because if MHT or TUS can reduce pain and improve function of the basal thumb joint, the significant disease burdens associated with pain and psycho-emotional stress, lost productivity, and frequent health care visits will also be reduced.

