
## Methods

### Study design

This is a single-center, randomized, controlled, repeated-measures, three-armed, parallel-group study conducted at the Waldfriede Hospital Berlin. Recruitment started in October 2019 (ClinicalTrials.gov identifier: NCT04115085). Patients are recruited from our hand surgery outpatient clinic on the Waldfriede Hospital campus. Further recruitment strategies include specific study calls on the website of the Waldfriede Hospital and information events and lectures for patients including distribution of study flyers. We intend to randomize 150 OAT patients to one of three hand therapeutic interventions. Intervention groups are (A) MHT with 18 sessions over 9 weeks, and (B) therapeutic TUS with 18 sessions over 9 weeks, and (C) combination therapy with MHT directly followed by TUS with 18 sessions over 9 weeks. Participants are studied on the first day before the intervention starts and at 9, 13, 17 and 33 weeks after the start of the intervention. The institutional review board of Waldfriede Hospital Berlin gave a positive evaluation for the study and written informed consent was obtained from all participants prior to study entry (Additional files 1 and 2). The study is conducted in accordance with the Declaration of Helsinki in its currently applicable version, the guidelines of the International Conference on Harmonization of Good Clinical Practice (ICH-GCP) and applicable German laws. Table 1 and Fig. 1 show the visit schedule and the study flow chart, respectively. Participants do not receive remuneration. For further details refer to the SPIRIT checklist (Additional file 2).

**Table 1 Tab1:** SPIRIT SUR study schedule

Visit	-1 Screening	0 Baseline Start intervention	1 End of intervention	2 Follow-Up	3 Follow-Up	4 Final follow-up visit
Week	−12 (max)	1	9	13	17	33
Informed consent	x					
Demographics	x					
Inclusion / exclusion criteria	x	x	x	x	x	x
Case history	x					
Medication	x	x	x	x	x	x
DASH		x	x	x	x	x
SF-36		x	x	x	x	x
VAS pain		x	x	x	x	x
Key pinch force		x	x	x	x	x
Goniometry		x	x	x	x	x
MHT		x	x			
TUS		x	x			
MHT + TUS		x	x			
Physical examination	x				x	
AE / SAE query		x	x	x	x	x

*AE* adverse event, *DASH* Disabilities of the Arm, Shoulder, and Hand, *MHT* multimodal hand therapy, *SAE* serious adverse event, *SF-36* Short Form 36, *SPIRIT* Standard Protocol Items: Recommendations for Interventional Trials, *SUR* Study of Medical Ultrasound for Rhizarthrosis, *TUS* therapeutic ultrasound, *VAS* visual analogue scale

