### Outcome parameters

Primary outcome is the change in the disease-specific Disabilities of the Arm, Shoulder, and Hand (DASH) questionnaire score after 9, 13, 17, and 33 weeks compared to baseline [41, 42].

Secondary patient-reported outcomes include: (1) VAS pain determined by change in distance between the patient-made mark after 9, 13, 17, and 33 weeks compared to baseline; (2) Short Form 36 (SF-36) determined by scale score change after 9, 13, 17, and 33 weeks compared to baseline [43]. Secondary disease-related outcomes include: (3) Thumb force or key pinch force evaluation, determined by change in Kg after 9, 13, 17, and 33 weeks compared to baseline. All thumb force evaluations will be assessed in the following position: Thumb on top of the radial side of the index finger below. (4) Goniometry measurement determined by change in range of motion after 9, 13, 17, and 33 weeks compared to baseline. All goniometric evaluations assess the active range of motion (ROM) of the angle between the dorsal axis of the thumb and the index finger with a manual goniometer.

All clinical assessments will be performed by the same experienced evaluator at all time intervals, who is blinded to the treatment allocation.

For safety monitoring, patients will be asked for tolerability of the interventions and in case of AEs a medical doctor is always at our site to provide help. For a detailed overview of assessments and endpoints see Table 1.

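### The within-group Friedman test names only the four post-baseline visits, so as written it cannot assess change from baseline

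*Protocol article*

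**What the plan says.** The Data analysis section of the protocol article separates two kinds of test.

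- **Between groups:** differences "regarding the primary endpoint are analyzed with the non-parametric Kruskal-Wallis test for independent samples", followed by pairwise Mann-Whitney tests.
- **Within groups:** the test named is Friedman's, and the sentence that assigns it begins: "The evaluation of intra-group differences (DASH or other characteristics after 9, 13, 17, and 33 weeks) is carried out by means of".

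The same section plans means, standard deviations and 95% confidence intervals for continuous data. It treats p < 0.05 as significant in an exploratory sense, without multiplicity adjustment.

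The Outcome parameters section defines the primary outcome as change in the DASH "questionnaire score after 9, 13, 17, and 33 weeks compared to baseline", and defines the secondary outcomes at the same visits. The Study design section describes five assessments: "Participants are studied on the first day before the intervention starts and at 9, 13, 17 and 33 weeks after the start of the intervention". Table 1 schedules DASH and VAS pain at baseline and at all four later visits, and places the end of intervention at week 9.

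All three arms receive active treatment: "Interventions are (1) multimodal hand therapy (2) therapeutic ultrasound, and (3) combination therapy with both hand therapy and ultrasound therapy". The Blinding section calls the study open-label. Entry requires VAS pain of at least 40 mm in pain phases over the last 24 hours. There is no DASH threshold.

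**The concern.** A reader expects a within-group test in a before-and-after setting to ask whether patients improved from baseline. The levels listed for this one are week 9 (end of treatment) and three follow-ups. A test over those levels asks only whether scores move between week 9 and week 33. A treatment that works by week 9 and holds its effect gives a null result. A significant result means that scores drifted after treatment, possibly because benefit was lost.

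The within-group result may attract attention. With three active arms, similar improvement in all of them leaves Kruskal-Wallis and Mann-Whitney with little to show. The within-arm test is then the one that seems to speak to the Introduction's hope for patients "if MHT or TUS can reduce pain and improve function of the basal thumb joint". As listed, it cannot address that. Once baseline is added it can detect change, but a within-arm change is still not a treatment effect, because nothing in the arm separates treatment from natural course, expectation or selection on a high pain score.

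**Working it through.** **1. The plan's own figure.** The Power calculation section gives 45 evaluable patients per group, 10% dropout and 50 enrolled: 45 / (1 − 0.10) = 50, and 3 × 50 = 150. This reproduces. No effect size, SD or correlation is stated, so those used below are assumptions. I use n = 45 per arm and the stated two-sided 0.05.

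**2. Raw scores or changes make no difference.** Let y_ij be patient i's score at visit j, and b_i the baseline. The change is d_ij = y_ij − b_i. For two visits j and k, d_ij < d_ik exactly when y_ij < y_ik, since b_i cancels. The ranks within each patient are identical, and so are the Friedman statistic and p-value. In simulation the largest difference between the two p-values was 0.

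**3. A sustained shift cancels in the same way.** If all four visits are lowered by the same amount δ, then (y_ij − δ) < (y_ik − δ) exactly when y_ij < y_ik. The four-visit rejection rate therefore cannot depend on δ. It stays at the nominal level.

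**4. Simulated rejection rates.** Normal data, n = 45 in one arm, equal correlation between visits, shift present at all four post-baseline visits, 3,000 runs per row. The Monte Carlo standard error near 5% is √(0.05 × 0.95 / 3000) ≈ 0.4 percentage points.

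| Correlation | Sustained shift (SD) | Four visits, as listed | Five visits, with baseline |
|---|---|---|---|
| 0.5 | 0 | 4.9% | 4.5% |
| 0.5 | 0.3 | 4.1% | 39.9% |
| 0.5 | 0.5 | 3.9% | 85.6% |
| 0.5 | 0.8 | 4.6% | 99.9% |
| 0.7 | 0 | 4.4% | 4.5% |
| 0.7 | 0.3 | 4.9% | 61.3% |
| 0.7 | 0.5 | 5.0% | 98.5% |
| 0.7 | 0.8 | 5.5% | 100% |

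By step 3, the scatter in the four-visit column is not an effect of the shift.

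**5. What a within-arm change would mean once baseline is included.** Suppose there is no true change and patients are selected on VAS ≥ 40 mm. If the threshold acts on the baseline value itself, the expected apparent fall is

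(1 − r) × SD × φ(z) / (1 − Φ(z)), with z = (40 − mean) / SD.

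For an assumed source mean of 40, SD 20 and r = 0.5: z = 0, φ/(1 − Φ) = 0.798, so 0.5 × 20 × 0.798 = 8.0 mm. For mean 60, SD 20 and r = 0.7: z = −1, φ/(1 − Φ) = 0.288, so 0.3 × 20 × 0.288 = 1.7 mm. Simulation (1,500 runs each, SD 20) gave:

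| Source mean | r | Apparent fall, threshold on baseline value | Five-visit rejection, threshold on baseline value | Five-visit rejection, threshold on separate earlier value |
|---|---|---|---|---|
| 40 | 0.5 | 8.0 mm | 75% | 4.1% |
| 40 | 0.7 | 4.8 mm | 46% | 4.9% |
| 50 | 0.5 | 5.1 mm | 31% | 5.5% |
| 50 | 0.7 | 3.1 mm | 18% | 5.1% |
| 60 | 0.5 | 2.8 mm | 11% | 4.2% |
| 60 | 0.7 | 1.8 mm | 9% | 5.5% |

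In the last column the earlier value has independent error, and the mean fall was about 0 mm in every row.

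**6. Which case applies is open.** The Table 1 row "Inclusion / exclusion criteria" is ticked at screening, at baseline and at every later visit. VAS is first scheduled at baseline and not at screening. Selection on the baseline value is therefore plausible but not established.

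**The case against.** **Baseline may be intended.** The visit list stands in a parenthesis. The Outcome parameters section uses the same four visits and measures each against baseline, so the parenthesis may be shorthand. This stands to the extent that no sentence says baseline is left out, and a reader who infers a deliberate exclusion goes beyond the text. It does not rescue the wording: ranking changes from baseline over the same four visits gives the same p-value. Nor is this a detail left to another document, since the article states both the test and the visits.

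**An improvement would still be visible.** The planned means and 95% confidence intervals would partly show it. That stands. One might infer that the trial would report effective treatment as no change; the documents do not say so. The risk is a misleading p-value beside informative summaries.

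**Within-group p-values are not claimed as efficacy.** One might infer that the sponsor means to read them that way. No sentence says so. The first stated aim is a direct comparison of treatments, p-values are called exploratory, and the Introduction's remark on reducing pain is a conditional statement about patient benefit.

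**Regression to the mean is not certain.** One might infer that improvement without treatment effect is to be expected, or that the main result is biased. Neither is supported. The size depends on assumed parameters and on which VAS value selects patients. The criterion concerns pain phases, which need not be the same quantity as the outcome VAS. DASH has no threshold and is affected only through its correlation with VAS. Randomised between-group comparisons are not biased by it.

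**Conclusion.** The point holds for the test as worded. Over weeks 9, 13, 17 and 33 the Friedman test has only chance-level rejection (about 4–5.5% in simulation with 45 per arm) for an improvement reached by week 9 and held, whether raw scores or changes are ranked. That result follows from the ranking itself and does not rest on the assumed correlation or effect size. The power gained by adding baseline (40–61% at 0.3 SD, 86–98.5% at 0.5 SD) does rest on those assumptions.

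The accompanying caution is conditional. Apparent VAS improvement of about 2–8 mm from selection alone is possible if the 40 mm threshold acts on the baseline value, and about 0 if it acts on a separate earlier value with independent error. With no untreated or sham arm and open-label treatment, within-arm change is not evidence of efficacy in either case.

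The consequence is limited: this is a supplementary exploratory analysis, and the randomised comparison of the primary endpoint is untouched. It should still be corrected before analysis, because the stated test cannot answer the natural within-group question.

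**What to change.** In the Data analysis section, do one of the following:

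- name baseline as a fifth level of the Friedman test, alongside weeks 9, 13, 17 and 33; or
- replace the test by an estimate, per arm, of change from baseline to each visit with a 95% confidence interval.

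If a test of stability after treatment is also wanted, keep the four-visit version and describe it as that.

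Add one sentence stating that within-group results are descriptive and that efficacy conclusions rest on the randomised between-group comparisons. Give the reasons: no untreated or sham arm, open-label treatment, and an entry threshold on VAS pain. State also whether that threshold is applied to the baseline VAS or to an earlier value.

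The cost is wording only, since DASH and VAS are already collected at baseline. A mixed model is optional and not needed for this; the protocol contains none, so adopting one would be a change of method. The downside for the sponsor is that within-arm significance can no longer be presented as evidence of efficacy.
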